## Methods and design

This study will be a randomized, placebo controlled, double blinded pilot superiority phase 2 trial. The rationale for choosing a randomized, placebo control trial is to avoid bias in patient allocation-to-treatment and increase the probability that any differences between groups can be attributed only to the treatment. This study is a pilot study given that there is limited to no data that currently demonstrates curcumin as an effective treatment for asthma.

Recruited subjects will undergo a screening process to ensure they meet the following study criteria listed in Table 1.

**Table 1 Tab1:** Inclusion and exclusion criteria for the study

Inclusion criteria	Exclusion criteria
Male or female, aged 18 and older Physician diagnosed moderate to severe asthma: (GINA 2018) Stable asthma that requires ICS/LABA and/or an additional controller agent (i.e. LTRA, LAMA) Ability to take oral medication and be willing to adhere to the regimen Ability to speak and read English If female and sexually active, should use effective forms of birth control	Current use of turmeric (curcumin) or use within the last 7 days Current use of biologic therapy/immunotherapy/ or bronchothermoplasty Pregnancy or lactation Known allergic reactions to components of turmeric (curcumin) Current use of anticoagulants, and history of coagulopathy or liver disease INR greater than 2.0, PTT greater than 45.0 s

*GINA* Global initiative for asthma, *ICS* inhaled corticosteroids, *LABA* long-acting beta agonist, *LTRA* leukotriene receptor antagonist, *LAMA* long acting muscarinic, *INR* international normalized ratio, *PTT* partial thromboplastin time

All subjects will be screened to ensure meeting inclusion criteria. Screening failure is attained when a participant consents to participate but is not subsequently randomly assigned to either the study intervention or control. In addition, any individual who does not meet the criteria for participation due to meeting exclusion criteria (screening failure) maybe rescreened. Rescreened participants will be assigned the same participant number as for the initial screening.

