### Design

After screening and meeting inclusion and exclusion criteria, subjects will be randomized 1:1 to one of two arms: (1) placebo (n_1_ = 15) or (2) intervention (n_2_ = 15), curcumin. Once assigned into their group, subjects will receive double-blinded study medication to take daily for 12 weeks. In total, subjects will have up to 6 clinic visits: screening visit (D-7 to -1), a baseline visit (V1), three monthly clinic visits (V2-4) and a follow-up clinic visit or phone-call (week 16).

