### Data analysis

Assuming a 30% attrition rate, a sample size of 30 participants is estimated using a moderate effect size for the group x time interaction (f = 0.25 or partial η^2^ = 0.06), level of significance (α = 0.05), and power of 0.80. Effect size was calculated using GPower software (version 3.1.2, University of Dusseldorf, Dusseldorf, Germany).

Data will be summarized using mean and standard deviation for quantitative variables and counts (%) for qualitative variables. The normality of continuous variables will be examined using Shapiro Wilk’s test. The distribution of the participants’ characteristics by study group will be evaluated using chi-square for qualitative variables and independent t- test for quantitative variables. A 2-groupX 4-time points (baseline, week 4, week 8, and week 12) mixed factorial analysis of variance (ANOVA) will be used to examine changes in asthma control test scores, number of days missed from school/work, FEV1 (% predicted), FEV1/FVC ratio, FVC (% predicted), blood eosinophil count, blood total IgE, and FeNO levels by group over time.

There will two main analyses that will be conducted in this study. First: a comparison between study groups will be conducted by looking at group x time interaction effect. The interaction will be evaluated and if there is a statistical significance, an independent t-test will be used by comparing change from baseline between groups at each follow up. A post-hoc Bonferroni test will be conducted for the combined groups if the main effect of time in the mixed factorial found to be significant. Second: A one-way repeated measures, ANOVA, will be used for within-groups to test changes from baseline at each time point. A post hoc testing using Bonferroni test will be used on each group separately if the results of the one-way repeated measures, ANOVA, is found to be statistically significant.

The level of significance will be set at *p* ≤ 0.05. Statistical analysis will be performed using IBM SPSS Software version 25 for Windows (Chicago, IL, USA).

Safety endpoints will be analyzed as summary statistics during treatment. Adverse Events (AEs) will be counted once only for a given participant), presented by severity, frequency, and relationship of AEs with additional information regarding cumulative dosing. Adverse events leading to premature discontinuation from the study intervention and serious treatment-emergent AEs will be presented either in a table or a listing.

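### Within-arm ANOVAs share main-analysis status with the between-arm interaction and do not depend on it, so a curcumin-only significant result can be read as efficacy when the arms do not differ

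*Protocol article*

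**What the plan says.** The Methods and design section sets the frame: "This study will be a randomized, placebo controlled, double blinded pilot superiority phase 2 trial". It justifies the placebo control as a way to "increase the probability that any differences between groups can be attributed only to the treatment". The Design section gives the arm sizes: "subjects will be randomized 1:1 to one of two arms: (1) placebo (n_1_ = 15) or (2) intervention (n_2_ = 15), curcumin".

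The Data analysis section then states: "There will two main analyses that will be conducted in this study". They are:

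- **Between arms.** "First: a comparison between study groups will be conducted by looking at group x time interaction effect". Independent t-tests of change from baseline between groups at each follow-up are run only if this interaction is significant.
- **Within arms.** "Second: A one-way repeated measures, ANOVA, will be used for within-groups to test changes from baseline at each time point". Bonferroni post-hoc testing "will be used on each group separately if the results of the one-way repeated measures" ANOVA are significant. The condition is that arm's own ANOVA, not the interaction.

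A Bonferroni post-hoc test on the combined groups follows if the main effect of time is significant. All tests use p ≤ 0.05. The sample size of 30 is built on the interaction alone (f = 0.25, power 0.80, 30% attrition). The section gives the two main analyses no order of precedence beyond listing the interaction first. It does not call the within-arm tests descriptive, and it does not say which analysis carries the efficacy conclusion.

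**The concern.** The second main analysis does not use the control arm. A change from baseline in the curcumin arm contains any drug effect together with placebo response and the effect of closer follow-up, and a one-sample analysis cannot separate them. Running the same test in the placebo arm and comparing the two verdicts does not help, because one p-value below 0.05 and one above is not evidence that the arms differ.

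The gating makes this worse. If the interaction is null, the visit-level between-arm t-tests are not run. The visit-level within-arm tests still are, wherever that arm's own ANOVA is significant. In the case where randomisation shows no difference, the only arm-specific visit-level p-values left are the uncontrolled ones, and they come from an analysis the plan calls main. What is at stake is the conclusion that a placebo-controlled superiority trial may draw.

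**Working it through.** **Inputs from the protocol article.** 15 per arm (Design). Four visits: baseline and weeks 4, 8 and 12; significance at p ≤ 0.05; 30% attrition (all Data analysis). With 30% lost and not replaced, 15 × 0.7 = 10.5, so about 10 per arm.

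**Assumptions, not in the documents.** Both arms have the same true mean change d, in SD units, at all three post-baseline visits. The correlation ρ between visits is 0.5 or 0.8, with compound symmetry and normal data.

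**The plan's own figure.** The only figure is N = 30, for the interaction. With f = 0.25, four visits and ρ = 0.5, the usual noncentral-F calculation gives N = 24 (power 0.816), and 24/0.7 rounds up to 35. With ρ = 0.6 it gives N = 20, and 20/0.7 rounds up to 29. The correlation is not stated, so 30 is neither confirmed nor refuted. The present point does not depend on it.

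**Step 1: the ceiling.** The arms are independent. If they have identical true change, each within-arm ANOVA is significant with the same probability p. Then

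P(curcumin significant, placebo not) = p(1 - p).

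This is largest at p = 0.5, where it is 0.25. With equal arms and equal true change, the ceiling does not depend on the correlation, the number of visits or the type of outcome.

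**Step 2: p for the planned ANOVA.** Means of (0, d, d, d) have a sum of squares about their average of 0.75d². The within-arm F test has 3 and 3(n - 1) degrees of freedom and noncentrality

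λ = 0.75·n·d²/(1 - ρ).

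Example with n = 15, d = 0.5, ρ = 0.5: λ = 0.75 × 15 × 0.25/0.5 = 5.625, so p = 0.451 and p(1 - p) = 0.451 × 0.549 = 0.248.

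P(curcumin significant, placebo not), identical arms:

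| Common shift d | n = 15, ρ = 0.5 | n = 15, ρ = 0.8 | n = 10, ρ = 0.5 |
|---|---|---|---|
| 0 | 4.8% | 4.8% | 4.8% |
| 0.25 SD | 11.8% | 20.7% | 9.2% |
| 0.5 SD | 24.8% | 11.7% | 20.8% |
| 0.75 SD | 14.5% | 0.2% | 23.8% |
| 1.0 SD | 2.2% | below 0.1% | 11.3% |

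**Step 3: simulation check.** With 40,000 trials per setting at ρ = 0.5, the corresponding rates at 15 per arm were 4.8%, 11.4%, 24.7%, 14.6% and 2.2%. The interaction test rejected in 4.8% to 5.2% of trials across all settings at 15 and 10 per arm. At 15 per arm and 0.5 SD, the curcumin-only pattern together with a non-significant interaction occurred in 23.1%.

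**Step 4: outcomes not measured four times.** Table 2 schedules eosinophils and IgE only at baseline and week 12, so the four-visit calculation does not describe them. A paired comparison of two visits with n = 15 and ρ = 0.5 gives p = 0.438 at 0.5 SD and 0.713 at 0.7 SD, hence p(1 - p) = 24.6% and 20.5%. Days missed is a count, which a normal model represents poorly. For all of these the 25% ceiling from Step 1 still holds.

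**The case against.** The strongest reply is that the valid test is already in the plan. The interaction is listed first, it alone drives the sample size, and Methods and design ties attribution to differences between groups. The within-arm analysis is described only as testing changes from baseline. A reader might infer that the protocol intends to claim efficacy from within-arm significance. It never says so, and the harm needs a later misreading. This stands, and it lowers the severity. It does not remove the point, because the equal main status and the separate gating are stated text. A separate analysis plan might add an interpretation rule, but it would have to override this wording.

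A second reply concerns size. A reader might take the values near 25% as the expected error rate. The documents do not support that. They give neither a shared shift nor a correlation, and the rate falls to about 5% with no shift and below 1% where both arms are almost certain to be significant. Table 1 requires stable asthma and sets no threshold on the outcome measures, so regression to the mean is a weak argument for a large shared improvement. Placebo response and closer follow-up remain plausible. Nor should the chance that the two arms merely disagree, 2p(1 - p), be quoted as the risk: half of it is placebo-only significance, which cannot support a claim for curcumin.

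A third reply is that the post-hoc test on pooled time is a routine follow-up to a main effect and makes no curcumin claim. That is right. It need not be removed.

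**Conclusion.** The point holds as one of labelling and gating, and should be fixed. The plan gives an uncontrolled within-arm analysis the same main status as the randomised comparison, and lets it produce visit-level p-values when the between-arm ones are withheld. If the arms truly change alike, the curcumin-only pattern arises with probability p(1 - p) per outcome. That is at most 25%, and ranges from below 1% to about 25% over assumed common shifts of 0 to 1 SD and correlations of 0.5 to 0.8, against about 5% for the interaction test. The ceiling needs only equal, independent arms with the same true change. Where a given outcome falls below it rests on the assumed shift and correlation. The between-arm test itself is unaffected.

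**What to change.** In the Data analysis section, name the between-arm comparison as the only main (confirmatory) analysis, and state that efficacy conclusions rest on it alone. Relabel the within-arm repeated-measures ANOVAs and their Bonferroni tests as descriptive, preferably reported as mean change with 95% confidence interval in each arm. Omitting their p-values is a matter of preference once the label is in place. The post-hoc test on the combined groups may stay if it too is labelled descriptive. The change should be made before unblinding.

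The cost is wording only: no change to sample size, visits or data collection.

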### Dosing and administration

Subjects will be receiving curcumin 1500 mg or matching placebo by mouth twice daily for the study period, 12 weeks. Any missed or vomited doses will be skipped and resumed at the next scheduled time. Subjects will use a dosing calendar to record administration or missed doses. The reason for selecting this dose is that curcumin (at 20 mg kg^−1^ bodyweight) was reported to attenuate allergen-induced airway hyper-responsiveness in sensitized guinea pigs [8]. It has been reported that humans can tolerate a dose of curcumin as high as 12 g/day, without any toxic side effects [15]. Therefore, we hypothesize that a dose of 3000 mg curcumin daily may significantly improve asthma control and affect other biomarkers of inflammation.

Sabinsa corporation will be providing the study drugs, both curcumin and matching placebo. Curcumin formulation will include 95% curcuminoids with black pepper extract plus inert excipients. The placebo formulation will contain the same inactive excipients found in curcumin. Both formulations will be identical in appearance. All study drugs will be clearly labeled for use for only this protocol and will not be shared or used for any patients not enrolled in this protocol. All study drug labels will include, *“Caution: New Drug Limited by Federal Law to Investigational Use."* Upon dispensing study drug will be labeled for subject specific use to be administered at home as prescribed by the investigator. All outpatient labels will follow California state Pharmacy laws for prescription drugs and be identified in a blinded fashion.

Study drugs will be stored at room temperature in their original containers for the length of time as instructed by the manufacturer Sabinsa as per their stability testing. Study drugs will be stored per Federal regulations, securely in limited-access pharmacy area and separately from commercial products. Storage temperature will be monitored daily by IDS to ensure proper storage is maintained.

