### Follow up

At week 16, the subject will be called or will visit the clinic to evaluate for any adverse effects of the drug. For subjects that may discontinue or withdraw early, we will record the rationale on final visit or via telephone conversation and cumulative curcumin dosage at that time point.

Table 2 shows the schedule of activities subjects will undergo in this study from beginning to end. Once the subject complete all phases of the study, indicated in Table 2, they are considered as completed the study.

**Table 2 Tab2:** Schedule of Activities that study subjects will go through from beginning to end

Procedures	Screening Day-7 to -1	Enrollment/baseline Visit 1, Day 1	Study visit 2 Week 4	Study visit 3 Week 8	Study visit 4 Week 12	Follow up Week 16
Informed consent	X					
Demographics	X					
Medical history	X					
Randomization		X				
Administer study intervention		X				
Concomitant medication review	X	X	X	X	X	
Physical exam (including height and weight)	X	X			X	
Vital signs	X	X			X	
ACT Scoring/ Questionnaire		X	X	X	X	
Spirometry (FVC, FEV1)		X	X	X	X	
Blood studies (eosinophils, IgE)		X			X	
Exhaled nitric oxide		X	X	X	X	
INR and PTT		X				
Urine pregnancy test (*if applicable)*		X	X	X	X	
Adverse event review and evaluation		X	X	X	X	X
Complete Forms	X	X	X	X	X	X

*ACT* Asthma control test, *FVC* forced vital capacity, *FEV1* forced expiratory volume in 1 s, *IgE* immunoglobulin E, *INR* international normalized ratio, *PTT* partial thromboplastin time

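### The safety summary is worded as covering the treatment period only, so adverse events starting between the last dose and the week 16 contact are collected but, read literally, not summarised

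*Protocol article*

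**What the plan says.** All references are to the protocol article.

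- **Treatment period.** Design: "subjects will receive double-blinded study medication to take daily for 12 weeks". Dosing and administration gives the same length: "Subjects will be receiving curcumin 1500 mg or matching placebo by mouth twice daily for the study period, 12 weeks".
- **Safety follow-up.** Follow up: "At week 16, the subject will be called or will visit the clinic to evaluate for any adverse effects of the drug". In Table 2 the row "Adverse event review and evaluation" is marked at Visit 1, at weeks 4, 8 and 12, and at week 16. The only other row marked at week 16 is form completion.
- **Early stoppers.** For subjects who stop or withdraw early, Follow up adds that "we will record the rationale on final visit or via telephone conversation and cumulative curcumin dosage at that time point".
- **Safety analysis.** Data analysis opens its safety paragraph with "Safety endpoints will be analyzed as summary statistics during treatment". It then says adverse events are counted once per participant and "presented by severity, frequency, and relationship of AEs with additional information regarding cumulative dosing". It closes by saying that events leading to premature discontinuation and "serious treatment-emergent AEs will be presented either in a table or a listing".

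Nowhere does the article say that findings from the week 16 contact enter the safety summary.

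**The concern.** The collection schedule and the analysis window do not match. The trial adds a contact four weeks after planned dosing ends in order to ask about adverse effects, and the sentence setting the period of the safety summary then stops at the end of treatment. The article does not leave the window open for a later document to fill; it states one that ends before the last safety contact.

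Two things are at stake, both modest. First, the Background gives finding a safe adjunctive therapy as part of the trial's purpose, and the Discussion says that the dose exceeds those studied before and that piperine is added to raise bioavailability. A reader would expect the follow-up contact to inform the safety account. Second, while the passages disagree, whether post-treatment events are counted could be settled after the data have been seen.

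**Working it through.** The point rests on comparing passages, with simple calendar arithmetic to size the gap. It uses no sample size, power or alpha, and the plan states no figure that needs reproducing.

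**Step 1: inputs.**
- Planned end of dosing: week 12 (Design; Dosing and administration).
- Last adverse event review: week 16 (Follow up; Table 2).
- Analysis window: the treatment period (Data analysis, first safety sentence).

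**Step 2: length of the uncovered period for a subject who completes dosing.**
- Last review minus end of dosing: 16 − 12 = 4 weeks.
- As a share of the scheduled collection period: 4/16 = 25%.

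This is calendar time only. Weeks off drug are not equivalent to weeks on drug for the chance of an adverse event, so 25% is not an estimate of the share of events lost.

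**Step 3: subjects who stop early.** If the last dose is at week *s*, with *s* below 12, the treatment period ends at *s*, and any later collection lies outside the window. If such a subject is still contacted at week 16, the uncovered period is 16 − *s* weeks; for example, *s* = 8 gives 8 weeks. The section on discontinuation of study intervention equates stopping curcumin with leaving the study but also says the remaining procedures follow the protocol, so how long these subjects are followed is not certain. The sample size paragraph assumes 30% attrition, so early stopping is expected.

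**Step 4: which events the literal wording leaves out.** The phrase most naturally describes when an event occurs, not when it is reported.

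| Onset | First reported | Covered by the stated window? |
|---|---|---|
| On or before last dose | By week 12 | Yes |
| On or before last dose | Week 16 | Yes |
| After last dose | Week 16 | No, read literally |

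Only the third row is at issue.

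**Step 5: whether other wording closes the gap.**
- The adverse event sentence sets out how events are counted and displayed and gives no period. It can be read as inheriting the window of the sentence before it or as having no limit.
- Treatment-emergent could include a period after the last dose, but the article does not define it. It also qualifies only the serious events, so it cannot by itself bring in non-serious ones.

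The text therefore supports two readings, and nothing in the article chooses between them.

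**The case against.** The strongest reply is that this is loose wording and not a rule that discards data. The time limit is attached to safety endpoints in general, and the sentence dealing with adverse events has no limit. Taken with Table 2, week 16 events could go straight into that tabulation. The definition of treatment-emergent normally sits in a full protocol or analysis plan, neither of which is shown, and it may well run to the week 16 contact. Moreover, an on-treatment summary is a legitimate quantity, it applies equally to both arms, and the analysis is descriptive. Because the data are collected whatever the wording, nothing is irretrievably lost.

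Much of this stands. The missing definition is not itself a fault in a condensed article. What remains is that the one window the article does state ends before the last safety contact it schedules.

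A reader might infer three stronger things, none of which the documents support:

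- *That everything first reported at week 16 is dropped.* Late-reported events with onset on treatment still fall within the window.
- *That the adverse event rate in each arm is understated.* A count limited to the treatment period is a narrower quantity than a count through follow-up, not a biased version of it, and no distortion between arms is shown.
- *That one omitted event would move an arm's rate by 1/15 = 6.7 percentage points.* That holds for any single affected participant among 15 and says nothing about expected impact. The denominator is also uncertain, because the Replacements section allows subjects who were dosed and then withdrew to be replaced, so more than 15 per arm may be exposed.

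**Conclusion.** The point holds in a limited form. On the literal text, adverse events with onset after the last dose are collected but not summarised. For subjects who complete dosing this concerns the 4 weeks between week 12 and week 16; for those who stop early it starts at their last dose. The conclusion assumes that the first safety sentence governs the adverse event sentence that follows it, and that no definition outside the article extends the period. If either assumption fails, the matter reduces to unclear wording.

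The documents give no expected number of post-treatment events, so the consequence cannot be expressed as a count or a rate. The weight is minor: this is a reporting improvement with no effect on efficacy, sample size or error rates.

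**What to change.** Reconcile the Data analysis section with Follow up and Table 2. Replace the first safety sentence with wording such as: *Adverse events will be summarised by arm from first dose through the week 16 contact, with events starting after the last dose shown separately.* Use the same window for the table or listing of serious events, and say there what treatment-emergent means in relation to it.

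Showing post-treatment onsets separately keeps the on-treatment summary available to anyone who wants it. The cost is a sentence or two of analysis wording. The adverse event review at week 16 is already scheduled, so no visit, procedure or data item is added. The change should be made before unblinding, so that the choice of window cannot depend on the results.
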